### Referral After a Positive Test

The examination will be repeated for images that are of insufficient quality for clinical interpretation. Across both groups, ophthalmology referral will be provided for participants with DR of stages 2 to 4 or AMD of stages 3 to 4, whereas participants not meeting these severity thresholds will be advised to undergo regular annual follow-up examinations. Confirmatory diagnosis of DR and AMD will follow the Early Treatment Diabetic Retinopathy Study [16], AREDS scales [23], and Beckman Initiative Classification [23] (Textbox 1). At 8 weeks after screening, referral completion and diagnostic outcomes will be assessed through review of electronic medical records, hospital visit records, and, when necessary, telephone follow-up.

Textbox 1.Confirmatory diagnosis of diabetic retinopathy (DR) and age-related macular degeneration (AMD).Diabetic retinopathyAccording to the Early Treatment Diabetic Retinopathy Study severity scale [24], primarily diagnosed through fundus photography and indirect ophthalmoscopy to identify typical features such as microaneurysms, retinal hemorrhages, hard exudates, and cotton-wool spots (soft exudates).Fluorescein angiography is generally not used as a primary diagnostic tool; however, it may be used in the evaluation of macular ischemia, edema, or neovascularization to inform treatment strategies. It facilitates the verification of the location and extent of lesions.The severity of DR is categorized into 5 stages: no diabetic retinopathy (no DR, stage 0), mild nonproliferative diabetic retinopathy (NPDR; stage 1), moderate NPDR (stage 2), severe NPDR (stage 3), and proliferative diabetic retinopathy (PDR; stage 4).Age-related macular degeneration:According to the Age-Related Eye Disease Study severity scale [25], fundus photography and indirect ophthalmoscopy are primarily used to identify the location, size, and number of drusen.On the basis of the Beckman Initiative Classification [23], AMD is classified into 4 severity levels based on drusen size and pigmentary abnormalities: no AMD (stage 1), early AMD (stage 2), intermediate AMD (stage 3), and advanced AMD (stage 4).When necessary, fluorescein angiography and optical coherence tomography are used to detect the choroidal neovascularization associated with AMD, the presence of macular edema, and retinal pigment epithelium abnormalities.

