### Sample Size Estimation

The estimated prevalence of any DR (across stages 1-4) and AMD is 27% and 10%, respectively [29,30]. For this study, the sample size is calculated based on the assumption that 10% of patients with diabetes aged ≥20 years are diagnosed with clinically significant DR (stages 2 to 4) in the Department of Family Medicine and the Department of Geriatrics and Gerontology. Using AI-assisted diagnostic tools, the detection is assumed to increase to 15% [31].

In this real-world pragmatic setting, there was no prior evidence on the referral rates for eye disease screening in Taiwan. This study therefore assumed a referral rate of approximately 70% based on large-scale pragmatic screening trials of fecal occult blood testing and *Helicobacter pylori* stool antigen testing in Taiwan [20,21]. Accordingly, it is assumed that 70% of screen-positive individuals will be successfully referred to ophthalmologists for further examination and with a 2-tailed test, a type I error (α) of .05, and a type II error (β) of .10, the required sample size is 2612 participants (1306 per group). Approximately 870 participants are expected to be enrolled annually over an anticipated 3-year study period.

For patients aged ≥50 years in the Department of Family Medicine and the Department of Geriatrics and Gerontology in the NTUH, the prevalence of AMD is 5%, which is assumed to increase to 10% with the use of AI-assisted diagnostic tools. Assuming that 70% of the screening cases can be successfully referred to ophthalmologists and with a 2-tailed test, a type I error (α) of .05, and a type II error (β) of .10, the required sample size is 1650 participants (825 per group). Approximately 550 participants are expected to be enrolled per year.

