Although the study adopted a multicenter pragmatic design, randomization was conducted at the individual level. The AI instruments are assumed to perform consistently across different settings. Therefore, the primary analyses of the primary outcomes will be conducted as crude analyses without adjustment for potential differences in baseline characteristics or workflow processes between the study groups. Nonetheless, hospital site effects, physician-level variation, image quality, referral completion, and missing confirmatory diagnoses may have been imbalanced between groups during study execution in this pragmatic setting and could potentially confound the primary analyses. Therefore, subsidiary analyses will be conducted at both the participant and physician levels using predefined subgroup analyses to examine the consistency of screening effects across primary outcomes. These subgroups will include study site, image quality (participants with and without poor-quality images for which AI could not generate a report despite repeat testing), referral timeliness (with delayed referral defined as no referral within 2 mo), physician specialty (including family medicine and geriatric or gerontology care physicians), clinical setting (across the 4 participating hospitals), and participant-level characteristics (including age, sex, and comorbidities). These subsidiary analyses are exploratory in nature, and results will be presented descriptively without adjustment for multiple comparisons.

In addition to the originally planned 2-sample proportion comparisons in the randomized trial and subsidiary stratified analyses, post hoc multivariable regression models will be performed to account for potential clustering and confounding factors and to support the findings from the primary analyses. Site-level variability and physician-level effects will be addressed using mixed-effects models, with study site and/or physician included as random effects where appropriate. Adjustment for relevant covariates, including baseline characteristics of patients, image quality, referral completion status, and missing confirmatory diagnoses, will also be performed. Effect estimates will be reported as adjusted odds ratios with corresponding 95% CIs.

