In addition, regarding the incomplete referral follow-up and missing confirmatory diagnoses in the pragmatic setting, the number and proportion of participants with missing outcome data will be summarized by study group, together with the reasons for missingness whenever available. The primary detection rate analysis will follow the intention-to-screen principle, in which screen-positive participants with missing confirmatory diagnosis will remain in the denominator but will not contribute to the numerator. For PPV analyses, participants with missing confirmatory diagnosis will be excluded from both the numerator and denominator. Post hoc mixed-effects regression analyses will be performed for these 2 outcomes accounting for other covariates as mentioned earlier.

A 2-sided *P* value of <.05 will be considered statistically significant. All statistical analyses will be conducted using the SAS software (version 9.4; SAS Institute).

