### Limitations

Although this study is designed as a low-risk pragmatic clinical trial, several limitations should be acknowledged. First, while detection rate and PPV provide meaningful indicators of real-world screening effectiveness and downstream care engagement, they do not capture all dimensions of screening accuracy or long-term patient benefit. Important outcomes such as false-negative rates, disease progression, visual outcomes, and treatment-related outcomes are not designated as central end points in this protocol. These outcomes represent important areas for future investigation beyond the scope of the current pragmatic trial. Nonetheless, these will be estimated using the simulation models. Second, follow-up data may be incomplete for participants who seek subsequent ophthalmologic care outside the NTUH health care system, Fu Jen Catholic University Hospital, and Min-Sheng General Hospital. In such cases, confirmatory diagnostic results and downstream clinical outcomes may not be fully captured, potentially limiting the completeness of outcome assessment. This issue will be evaluated in the subgroup analyses. Third, the AI-assisted screening tools evaluated in this study are designed to detect specific retinal conditions only, including the DR and AMD. Other ocular diseases or retinal pathologies are not within the diagnostic scope of these tools and therefore may not be identified through the AI screening process while they may be identified by physicians. These will be evaluated in the post hoc analyses. Fourth, suboptimal image quality and inherent limitations in AI-based interpretation may result in false-positive or false-negative screening results, which could lead to unnecessary referrals or missed cases. To reduce this risk, image quality will be monitored at the time of acquisition, with repeat imaging performed when necessary, and cases with uncertain findings will still be referred for ophthalmologic evaluation. The impact will be evaluated in the subgroup or post hoc analyses. Fifth, real-world health care system constraints may influence the effectiveness of the screening-to-referral pathway. Limited ophthalmology workforce capacity and outpatient clinic availability may affect referral completion and time to confirmatory diagnosis, particularly in high-volume clinical settings. These constraints reflect routine clinical practice and may impact the generalizability of study findings to health care systems with different resource availability. Finally, it is important to emphasize that the AI-assisted screening tools are intended to support, rather than replace, clinical judgment. Treating physicians and ophthalmologists retain full responsibility for diagnostic confirmation and treatment decisions. Medical personnel involved in the study will receive training on appropriate interpretation and use of AI-assisted outputs to ensure safe and effective integration into clinical care.

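### The detection rate mixes screening yield with referral attendance, and the stated remedies for unequal attendance cannot show whether a detection gain survives it

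*Protocol article*

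**What the plan says.** Primary Outcome and Statistical Analysis apply the same rule to the detection rate: "screen-positive participants with missing confirmatory diagnosis will remain in the denominator but will not contribute to the numerator". The primary comparison is a crude two-sample test of proportions in everyone randomised. For PPV, unconfirmed screen-positives are left out of both numerator and denominator.

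Sample Size Estimation assumes that 70% of screen-positives reach an ophthalmologist, so about 30% are expected to stay unconfirmed. Under Referral After a Positive Test, status is established at 8 weeks "through review of electronic medical records, hospital visit records, and, when necessary, telephone follow-up".

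Statistical Analysis acknowledges that referral completion and missing confirmatory diagnoses may be imbalanced between arms and could confound the primary analyses. It offers two remedies:

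- Subgroups, including "referral timeliness (with delayed referral defined as no referral within 2 mo").
- Post hoc mixed-effects regression with referral completion status and missing confirmatory diagnosis among the covariates.

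Limitations adds that "follow-up data may be incomplete for participants who seek subsequent ophthalmologic care outside" the participating hospitals, and answers: "This issue will be evaluated in the subgroup analyses".

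Two descriptive items also bear on the point: missing outcome data summarised by study group, with reasons where available (Statistical Analysis), and referral completion rate (Exploratory Outcomes).

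**The concern.** The aim and hypothesis concern earlier and better detection. The measured outcome also moves with attendance at ophthalmology and with whether the result is captured. If one arm attends more, its detection rate rises without a single additional diseased eye being flagged. If the AI arm attends less, a real gain in detection can be hidden.

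Unequal attendance is plausible. The trial is open-label. Principal Results says control-arm results are communicated at follow-up appointments and AI-arm feedback is timely, whereas the Intervention section calls the two workflows identical. Those passages need to be reconciled. A later result inside a fixed 8-week window could lower captured completion in one arm.

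The protocol sees the threat and commits to specific responses. If those responses cannot answer the question, a reader will take them as reassurance, or as refutation, that they do not provide.

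**Working it through.** **Inputs from Sample Size Estimation.** The design is set "with a 2-tailed test, a type I error (α) of .05, and a type II error (β) of .10". For DR, "10% of patients with diabetes aged ≥20 years are diagnosed with clinically significant DR (stages 2 to 4"), and with AI "the detection is assumed to increase to 15" per cent. For AMD the rates are 5% and 10%. Completion is 70%. The sizes are 1306 per arm (DR) and 825 per arm (AMD).

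**Reproducing the stated sizes.** Unpooled two-proportion formula, (1.960 + 1.282)² = 10.507:

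- DR: 10.507 × (0.10×0.90 + 0.15×0.85) / 0.05² = 914.1; divided by 0.70 = 1305.9, matching 1306.
- AMD: 10.507 × (0.05×0.95 + 0.10×0.90) / 0.05² = 577.9; divided by 0.70 = 825.6, against 825 stated.

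**What the primary test compares.** Let yield be the proportion who screen positive and would be confirmed if examined. If completion does not depend on true status, observed rate = yield × captured completion. At the planning values this is 7.0% v 10.5%, and the pooled z test at 1306 per arm has 88.6% power.

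**Equal yield, unequal completion.** The completion values are assumptions; the documents give no between-arm gap. With observed rates p0 and p1, difference d, null standard error s0 = √[2p̄(1−p̄)/n] and s1 = √{[p0(1−p0)+p1(1−p1)]/n}, the chance of significance favouring AI is Φ[(d − 1.96 s0)/s1]. Example, DR at 70% v 80%: rates 0.070 and 0.080, s0 = s1 = 0.0103, Φ(−0.99) = 0.161. Two-sided results:

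| Completion, control v AI | DR, yield 10%, n=1306 | AMD, yield 5%, n=825 |
|---|---|---|
| 70% v 80% | 16% | 8% |
| 70% v 85% | 30% | 12% |
| 60% v 80% | 52% | 20% |

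At yields midway between the planning rates, 60% v 80% gives 62% for DR (yield 12.5%) and 28% for AMD (7.5%). From 70% control completion at 10% DR yield, significance becomes the expected result only when AI-arm completion reaches about 91%. At 5% AMD yield it never does.

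**Reverse direction.** True DR yield 10% v 15%, completion 70% v 60%: observed 7.0% v 9.0%, power 47%, against 89% at equal completion.

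**Do the stated remedies separate the two causes?**

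- *Referral-timeliness subgroup.* Among screen-positives not referred within 2 months, with outcomes read at 8 weeks, detection is near zero in both arms by construction. The timely subgroup is selected after randomisation.
- *Adjusted regression.* No event can occur without a completed referral. Conditioning on completion therefore leaves only the comparison of confirmed to non-confirmed among attenders, which is PPV. I simulated this with assumed inputs: control 20% screen-positive, PPV 50% in both arms.
  - Attendance alone differs (70% v 85%): primary test favours AI in about 30% of trials; attenders-only contrast significant in about 5%.
  - True gain in yield from 10% to 15% (screen-positives 20% v 30%) at equal 70% completion: primary test about 89%; attenders-only contrast again about 5%.

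  In these scenarios the check reads null whichever cause is at work.
- *Outside care.* Limitations sends it to the subgroup analyses, but the listed subgroups are site, image quality, referral timeliness, physician specialty, clinical setting and participant characteristics. None identifies care received elsewhere.

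**The case against.** **The outcome is legitimate as programme yield.** Everyone randomised is analysed whatever their adherence, and Limitations presents the outcomes as reflecting downstream engagement with care as well as screening. If AI raises attendance and more people are confirmed, rejecting is correct. This stands. A reader might infer that the percentages above are an inflated type I error. They are not: they are power for a real difference in the outcome as defined. Only unequal capture of diagnoses made elsewhere would be bias in that outcome, and the documents give nothing to size it.

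**An imbalance would be visible.** A reader might infer that nothing planned would reveal unequal attendance. That is not supported: missing data are tabulated by study group, and referral completion would show it too if reported by arm. Screen-positive proportion times attenders' PPV could also be formed by arm from recorded data. But no planned analysis forms that contrast, and the descriptive items do not say whether a gain survives.

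**Imputation detail normally belongs in the SAP, which is not shown.** True, and its absence alone would be no finding. The point here is different: the protocol names its remedies, and those remedies condition on variables that determine the outcome. Labelling them exploratory or post hoc lowers their weight but does not make them informative.

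**No mechanism is documented.** Nothing says that patients receive an AI report; outputs go to physicians through the health record. The attendance gaps are assumptions, and most are too small to make significance the expected result, particularly for AMD.

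**Conclusion.** The concern holds in this form: the primary detection rate is an acceptable measure of programme yield, but it cannot by itself support a claim that AI detects more disease, and the protocol's remedies for unequal completion cannot fill that gap. Following them would give a supporting analysis that can read null whether or not AI raises yield.

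The size depends on attendance gaps that the documents do not give. For 10- to 20-point gaps at equal yield, a significant DR difference arises in 16% to 52% of trials and a significant AMD difference in 8% to 20%. A 10-point gap the other way roughly halves the power to show the planned DR gain. These figures assume that completion is unrelated to true disease status among screen-positives. The null behaviour of the adjusted check was simulated with PPV equal in both arms; if AI changes PPV, the check picks up that change, which is still not yield.

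This should be changed before analysis, but it does not undermine the primary outcome.

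**What to change.** - Keep the primary definition and test.
- Remove referral completion status and missing confirmatory diagnosis from the regression covariates, and do not use the referral-timeliness subgroup as a check on the detection rate.
- Report screen-positive proportion and referral completion by arm.
- Prespecify one sensitivity analysis for the detection rate: multiply impute the confirmatory result of unconfirmed screen-positives, separately by arm, from the recorded screening result, disease, site and age, with a tipping-point table. Physician interpretations and AI outputs are already recorded in REDCap. The AMD output separates only levels below 3 from 3 and above, so it will add little among AI-positives.
- State that an outside ophthalmologist's diagnosis documented at the 8-week follow-up counts as confirmed. The text appears to allow this already, so it is a clarification. In Limitations, replace the reference to subgroup analyses with the analysis above.
- Attribute a gain to detection rather than attendance only if it holds in that analysis.

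The cost is a little more analysis work and wording, with no extra participants or visits. The downside is a missing-at-random assumption in the imputation, which the tipping-point table tests.

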### Cost-Effectiveness Analysis

As long-term outcomes, such as blindness, require extended follow-up, their assessment is impractical, given the rapid evolution of AI-assisted diagnostic software and the frequent release of updated versions throughout the product life cycle. Therefore, a model-based cost-effectiveness analysis will be conducted to compare the AI-assisted screening strategy with conventional physician-based screening for DR and AMD. Clinical effectiveness inputs, including screening detection rates and referral outcomes, will be derived from the randomized trial. These natural course models are illustrated in Figure 6A (DR) and Figure 6B (AMD). The decision analysis will include two arms following the decision node: (1) usual care and (2) the AI-assisted model. A decision-analytic framework incorporating both a decision tree and a Markov model will be developed to simulate disease progression, downstream clinical management, and long-term health outcomes following screening (Figure 7). Health states will represent different stages of disease progression for DR and AMD, as well as blindness and death; therefore, extending the analysis beyond the eye disease screening process primarily evaluated in this trial.

**Figure 6. F6:**
[figure not shown]
Markov model structure. (A) The diabetic retinopathy (DR) Markov model consists of 7 mutually exclusive health states: no DR, mild nonproliferative diabetic retinopathy (NPDR), moderate NPDR, severe NPDR, proliferative DR, blindness, and death. Disease progression is assumed to be irreversible, with transitions allowed only from less severe to more severe states or remaining in the same nonabsorbing state (self-loops). Death represents all-cause mortality. (B) The age-related macular degeneration (AMD) Markov model includes 6 mutually exclusive health states: no AMD, early AMD, intermediate AMD, advanced AMD, blindness, and death. Transitions are assumed to be unidirectional, allowing progression to more advanced disease stages or remaining in the current state. Death represents all-cause mortality.

**Figure 7. F7:**
[figure not shown]
Decision-analytic framework for (A) diabetic retinopathy (DR) and (B) age-related macular degeneration (AMD) illustrating the decision tree structure for screening outcomes followed by downstream disease progression pathways under artificial intelligence (AI)–assisted and conventional screening strategies. NPDR: nonproliferative diabetic retinopathy.

At the screening stage, individuals will be classified as true positives, false positives, true negatives, or false negatives based on the diagnostic performance of each strategy. Patients identified as positive will be referred for confirmatory diagnosis and subsequent treatment, whereas those with negative results will not undergo further evaluation at that time. Individuals with false-negative results are assumed to experience delayed diagnosis and will follow the natural history of disease progression until clinical detection. Transition into the Markov model is determined by the initial screening outcomes, and health outcomes and costs associated with disease progression, vision impairment, and treatment will be accumulated over the analytic time horizon.

For DR, disease progression will be modeled using a Markov framework based on established natural history models [32-34]. Health states will include no DR, nonproliferative DR (mild, moderate, and severe), proliferative DR, blindness, and death. For AMD, health states will include no AMD; early, intermediate, and advanced AMD; blindness; and death. In both models, health states are mutually exclusive and collectively exhaustive. Disease progression is assumed to be irreversible, allowing transitions only from less severe to more advanced disease stages or remaining in the same nonabsorbing state (self-loops).

Patients with false-negative results (ie, individuals with DR or AMD not detected through screening) are modeled as following the natural history of disease progression until clinical detection, reflecting the impact of delayed diagnosis on both health outcomes and associated medical costs for treatment.

Cost estimation will be conducted from both the societal perspective and the National Health Insurance (NHI) payer perspective, a single-payer system. Costs considered will include direct medical costs (screening, follow-up visits, and treatments), indirect medical costs (information technology maintenance and health care workforce resources), and indirect costs (transportation and productivity loss due to visual impairment). The model will include screening costs, follow-up diagnostic costs, and direct medical costs associated with the diagnosis and treatment of DR and AMD. From the societal perspective, indirect costs, including transportation and productivity loss due to visual impairment, will also be incorporated.

All costs will be estimated in New Taiwan Dollars and, if applicable, converted to US dollars based on the average exchange rate for the study year of 2026. Cost parameters will be primarily derived from the Taiwan NHI reimbursement schedule [35], supplemented by institutional data. All these data will be obtained from the NTUH-integrated Medical Data Center [36].

As AI-assisted screening has not yet been reimbursed under the Taiwan NHI, the cost of AI-assisted screening will be estimated based on assumptions and expert consultation. Screening and follow-up diagnostic costs will be based on standard clinical practice and reimbursement policies under the NHI system. Treatment costs for DR and AMD will be estimated using a combination of NHI fee schedules and published sources. Where necessary, assumptions will be informed by expert opinion. After screening, individuals with true-positive results will incur costs related to screening, confirmatory diagnostic evaluation, and subsequent treatment. Those with false-positive results will incur screening and unnecessary referral costs, including additional ophthalmology visits and diagnostic procedures. True-negative cases will be assumed to incur screening costs only, with no further downstream costs. For individuals with false-negative results, costs will include initial screening costs as well as additional downstream costs associated with delayed diagnosis, disease progression, and subsequent treatment at more advanced stages. These cases may also incur higher long-term costs related to vision impairment and productivity loss. Costs and quality-adjusted life years (QALYs) will be discounted at 3%.

Quality-adjusted life years will be used to quantify health benefits and evaluate cost-effectiveness. QALYs integrate survival and health-related quality of life by weighting life years with health state utility values. In this study, QALYs will be calculated by multiplying the expected survival years by corresponding utility weights for each health state, with values ranging from 0 (blindness) to 1 (perfect health); negative values may be applied to health states perceived as worse than blindness.

QALY=years of life×health state weight

The primary outcome of the cost-effectiveness analysis is the incremental cost-effectiveness ratio, defined as the difference in costs divided by the difference in effectiveness between the 2 screening strategies. Given the limited duration of trial follow-up, a model-based economic evaluation using a Markov model will be conducted to project long-term costs and outcomes following screening. Detection rate will serve as the primary effectiveness measure.

$$ICER=\frac{\Delta cost}{\Delta effectiveness}=\frac{cost_{new}-cost_{old}}{effectiveness_{new}-effectiveness_{old}}=\frac{Incremental\;Cost\;}{\;incremental\;effectiveness\;}\;\left(common:cost\;per\;QALY\right)$$

To assess parameter uncertainty, one-way sensitivity analyses and probabilistic sensitivity analyses will be performed. Results will be summarized using cost-effectiveness planes and cost-effectiveness acceptability curves. The analyses will be performed using TreeAge Pro 2024 (TreeAge Software, Inc).

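### The QALY scale is anchored at 0 = blindness and leaves death without a value, which magnifies any QALY difference arising from blindness; separately, the ICER denominator is stated in two ways

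*Protocol article*

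**What the plan says.** All of this is in the protocol article, Methods, Cost-Effectiveness Analysis, including the legends of Figures 6 and 7.

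- **Purpose of the QALY:** "QALYs integrate survival and health-related quality of life by weighting life years with health state utility values", with the formula "QALY=years of life×health state weight".
- **Utility scale:** "values ranging from 0 (blindness) to 1 (perfect health); negative values may be applied to health states perceived as worse than blindness". No value is given for death.
- **DR model:** "Health states will include no DR, nonproliferative DR (mild, moderate, and severe), proliferative DR, blindness, and death".
- **AMD model:** "For AMD, health states will include no AMD; early, intermediate, and advanced AMD; blindness; and death".
- **Mortality:** the Figure 6 legend says "Death represents all-cause mortality" for each model.
- **Effectiveness measure:** the section says "Quality-adjusted life years will be used to quantify health benefits and evaluate cost-effectiveness". After defining the ICER as cost difference over effectiveness difference, it says "Detection rate will serve as the primary effectiveness measure". The ICER formula that follows is annotated as commonly being cost per QALY.
- **Uncertainty:** one-way and probabilistic sensitivity analyses are planned for parameter uncertainty. Costs and QALYs are discounted at 3%.

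**The concern.** Years multiplied by a weight measure survival and quality of life together only if a weight of zero means the same as not being alive. Here zero means blind. Blindness serves as the zero point twice in the same sentence, and nothing elsewhere in the article corrects it. Death is a separate state in both models, so a modeller following the text must either give death zero as well, or place it somewhere on a scale that does not mention it. Either way the incremental QALYs are wrong.

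The stakes are real. Cost-effectiveness is the only outcome listed under Secondary Outcomes, and the Introduction and Results tie it to insurance reimbursement. Blindness is the last disease state before death in both models, so its utility is a key input.

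A second, independent problem is the ICER denominator. Cost per case detected and cost per QALY are different quantities. A cost-effectiveness plane or acceptability curve needs one declared denominator.

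**Working it through.** **Plan's own figure.** The article states no utility, QALY total or ICER, so there is nothing to reproduce. The utilities below are assumptions on the death = 0 scale: sighted state 0.8; blindness 0.2, 0.4 or 0.6.

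**Step 1: correct gain per blind year averted** (death = 0) = u_sighted − u_blind.
- 0.8 − 0.2 = 0.6
- 0.8 − 0.4 = 0.4
- 0.8 − 0.6 = 0.2

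**Step 2: blindness set to 0, death also 0, other states unchanged.** The credited gain is u_sighted − 0 = 0.8, so the overstatement is u_sighted / (u_sighted − u_blind).
- 0.8 / 0.6 = 1.33
- 0.8 / 0.4 = 2.0
- 0.8 / 0.2 = 4.0

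**Step 3: whole scale shifted so that blindness = 0 and full health = 1.** Each living state becomes (u − u_blind) / (1 − u_blind). With equal survival in the two arms, every QALY difference is multiplied by 1 / (1 − u_blind).
- 1 / 0.8 = 1.25
- 1 / 0.6 = 1.67
- 1 / 0.4 = 2.5

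**Step 4: does this carry through a whole model?** An illustrative DR cohort was run with the seven states of Figure 6, 30 yearly cycles and 3% discounting. All other inputs are assumptions:
- 10% of those screened have disease, starting 60% moderate, 25% severe and 15% proliferative.
- Utilities in those states are 0.83, 0.78 and 0.70.
- Annual mortality is 3%.
- Detection halves progression.
- Sensitivity is 0.9 with AI and 0.6 without.

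Incremental QALYs per 1000 screened:

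| Blindness utility | Death = 0 (correct) | Blindness and death both 0 | Whole scale shifted |
|---|---|---|---|
| 0.2 | 33.7 | 44.2 (1.31 times) | 42.1 (1.25 times) |
| 0.4 | 23.3 | 44.2 (1.90 times) | 38.8 (1.67 times) |
| 0.6 | 12.8 | 44.2 (3.45 times) | 32.0 (2.50 times) |

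The third column does not move, because the true utility of blindness no longer enters the result. With mortality doubled in the blind state, the factors in that column are 1.24, 1.62 and 2.34.

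**Step 5: direction.** With the sensitivities reversed (AI 0.6, usual care 0.9), the same factors magnify a loss. At a blindness utility of 0.4, −23.3 becomes −44.2. The error therefore amplifies whatever blindness difference the model produces. Sample Size Estimation assumes that AI raises detection from 10% to 15% for DR and from 5% to 10% for AMD, and the model sends missed cases along the natural history. Under those assumptions the amplification favours AI. For a fixed positive incremental cost, the ICER is then too low by the same factor.

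**Step 6: detection rate.** Using detection rate as the effectiveness measure changes none of the QALY figures above. It produces a different ratio, cost per additional case detected.

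**The case against.** The anchor may be a drafting slip for death, and a health economist building the model would probably use published utilities with death at 0. That is plausible, but the wording is explicit and repeated, and the article offers nothing to override it.

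It can also be said that death is simply not placed on the scale, and that the permitted negative values could hold it below blindness. A blind year then does not necessarily equal a dead one. This stands, and is why the point rests on death being unplaced. It does not rescue the scale: the shift in Step 3 still stretches every difference by 1 / (1 − u_blind), so the unit is no longer a QALY comparable with others.

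Sensitivity analyses are planned, but they vary inputs. On this scale blindness is 0 by definition, so they would not correct the anchor.

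A reader might infer several stronger things that the document does not support:
- **That the result is tilted toward AI whatever happens.** The direction depends on whether AI averts blindness. A lower ICER also requires a positive incremental cost, and the AI cost is still to be estimated.
- **That the overstatement reaches sevenfold.** This needs a sighted utility of 0.70 and a blindness utility of 0.60 (0.70 / 0.10 = 7), both assumed, with the sighted value left on the death = 0 scale while blindness is moved. Shifting the whole scale with blindness at 0.60 gives 2.5.
- **That naming detection rate biases the QALY result.** It does not (Step 6).
- **That lifetime costs are divided by a detection rate and the QALYs go unused.** No lifetime horizon is stated, and QALYs are to be discounted and used.

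Finally, the randomised primary outcomes, sample size and trial conduct are untouched.

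**Conclusion.** The anchor is a genuine error. As written, it gives wrong incremental QALYs whenever the arms differ in time spent blind. With assumed utilities of 0.8 (sighted) and 0.2 to 0.6 (blind), the overstatement per blind year averted is about 1.33 to 4.0 times if death is also 0. It is 1.25 to 2.5 times if the whole scale is shifted and survival is equal. The illustrative cohort gives similar ranges. All these sizes rest on assumed inputs; the existence of the error does not. It favours AI under the protocol's planning assumptions and would penalise AI if AI missed more cases.

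The ICER denominator is a separate contradiction. It leaves open which ratio is the primary economic result, without biasing the QALYs.

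**What to change.** 1. Redefine the scale: 0 = death, 1 = full health, with negative values only for states worse than death.
2. Give blindness its own sourced utility in the DR and AMD models, and vary it in the one-way and probabilistic sensitivity analyses.
3. Name one primary ICER. Cost per QALY is preferable given the Markov model and the reimbursement aim, with cost per additional confirmed case detected reported as a separate ratio. Making the latter primary would also remove the contradiction if stated explicitly.

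The cost is a change of wording and of the blindness utility before the model is run. Recruitment, data collection and the primary clinical analyses do not change. If AI does avert blindness at a positive incremental cost, the ICER will be less favourable to it than under the present scale.
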